### Sample size

As previously indicated, the principal variable is the BMI *Z* score, on which the sample size calculation was based. Its standard deviation is 2.29 in the least favorable case (according to the tables by Cole et al. [29]), and a desired minimum difference of 2 points is expected. With an *α* error of 0.05, a β error of 0.20 and an estimated follow-up loss of 20 %, four groups in total are planned for the study: two groups of obese children (pre-pubertal and pubertal) treated with metformin and two groups of obese children (pre-pubertal and pubertal) treated with a placebo; there is a requirement of at least 40 patients per group (× four groups = 160 children total).

The clinical argument for the choice of the principal variable adheres to the fact that the obesity concept is based on the BMI, as the bibliography endorses. However, it should be noted that the BMI in childhood changes substantially with age [30]. Thus, age- and sex-specific cut-off points are needed to define pathology in children via means of a *Z* score [29] to obtain a more accurate value.

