**Discussion:**

This study will assess the differential response of metformin treatment at six months in pre-pubertal and pubertal obese children.

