### Outcome measures

#### Anthropometry

Body weight (kg), height (cm) and waist circumference (cm) are measured via standardized procedures. The BMI and BMI *Z* score are calculated based on Spanish reference standards published by Sobradillo et al. [31]. Obesity is defined according to the BMI, with the age and sex-specific cut-off points proposed by Cole et al*.* [29] (BMI >95th percentile). Anthropometric measurements are obtained by a single examiner with the children barefoot and in their underwear. To obtain data on body composition, fat mass, lean mass and total body water are measured via bioimpedance technology using Tanita B18.

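### The sample-size inputs (SD 2.29, difference 2 points) are not credible for the BMI Z score, and they give 27–28 per group rather than the stated 40

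*Protocol article*

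**What the plan says.** The Sample size section of the protocol article names the BMI Z score as the principal variable, "on which the sample size calculation was based". It then gives the inputs:

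- SD: "Its standard deviation is 2.29 in the least favorable case", credited to the international tables (reference 29).
- Difference: "a desired minimum difference of 2 points is expected".
- Error rates: "error of 0.05, a β error of 0.20", with no sidedness and no multiplicity adjustment.
- Follow-up loss: 20 %.
- Result: for four groups (puberty by treatment), "there is a requirement of at least 40 patients per group", 160 in all.

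Three other places bear on these inputs. Table 2 admits only children with BMI above the 95th percentile. The Anthropometry section says that the BMI and BMI Z "score are calculated based on Spanish reference standards" (reference 31). The Statistical analysis section tests treatment through its interaction with time, that is, through change.

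**The concern.** A Z score is expressed in SD units of its reference population, where its SD is 1 by construction. An SD of 2.29 and an expected difference of 2 units do not look like quantities on that scale. They look like kg/m², although the section says they belong to the Z score. If so, the planned effect and variability describe a different variable from the primary endpoint.

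The stated result also does not follow from the stated inputs, so a reader cannot tell which comparison, error rate or adjustment the 40 was meant to serve.

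At stake is the reading of the result. The article calls for adequately powered trials and attributes an earlier null finding on puberty to small numbers. Without a valid detectable difference on the BMI Z score, a null result here would be equally hard to interpret.

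**Working it through.** **1. Reproducing the 40.** Inputs as stated, two-sided alpha assumed, two groups of equal size:

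n = 2 (z₀.₉₇₅ + z₀.₈₀)² SD² / Δ² = 2 × (1.96 + 0.8416)² × 2.29² / 2² = 20.58, so 21 evaluable per group. The exact t-test version gives 22.

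Allowing for 20 % loss: 21 / 0.8 = 26.3, so 27; 22 / 0.8 = 27.5, so 28. Four groups would total 108–112, not 160.

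Variants tried:

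| Variant | Evaluable per group | After 20 % loss, n/0.8 |
|---|---|---|
| Two-sided 0.05, 80 % power | 21–22 | 27–28 |
| One-sided 0.05, 80 % power | 17 | 22 |
| Two-sided 0.05, 90 % power | 28–29 | 35–37 |
| Four-group ANOVA, three mean patterns | 16–30 | 20–37 |
| 2-point interaction contrast | 42 | 53 |
| Bonferroni over 6 pairs, normal approximation | 31.75, so 32 | 40 |
| Bonferroni over 6 pairs, exact t | 34 | 43 |

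Only the six-pair Bonferroni correction with the normal approximation gives 40 at 80 % power. The Sample size section does not mention it; Bonferroni appears only in the Statistical analysis section. The match is not unique either. Two comparisons at 90 % power with loss added as n × 1.2 give 33 × 1.2 = 39.6, also 40, though that contradicts the stated beta.

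**2. Power of the planned size on the stated inputs.** With 40 × 0.8 = 32 completers per group and d = 2 / 2.29 = 0.873, power is 93 % (t) to 94 % (normal). The plan's own inputs therefore exceed its 80 % target.

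**3. Scale check.** Assume a normal reference and one reference for entry and outcome. The 95th percentile is z = 1.645. The distribution above it has mean about 2.06 and SD about 0.37. If the placebo arm stays at its baseline, a 2-unit difference takes the average treated child to 2.06 − 2 = 0.06, about the reference mean. Both arms receive lifestyle advice, so this would be the effect of metformin over and above it. If the SD were 1.0 and the difference really 2, n = 2 × 2.8016² × 1² / 2² = 3.9, so 4 per group would suffice.

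**4. Power on a Z scale.** The documents give no SD of change and no Z-scale effect. Both are assumptions here, shown as a range, with 32 completers per group:

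| Assumed SD | Δ = 0.2 | Δ = 0.3 | Δ = 0.5 |
|---|---|---|---|
| 1.0 | 12 % | 22 % | 52 % |
| 0.5 | 36 % | 67 % | 98 % |
| 0.3 | 76 % | 98 % | >99 % |

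**5. What 32 completers per group detect, in SD units** (80 % power, two-sided 0.05):

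- Within a pubertal stratum: 2.8016 × √(2/32) = 0.70 SD.
- Overall, 64 per arm: 2.8016 × √(2/64) = 0.50 SD.
- Treatment-by-puberty interaction: 2.8016 × √(4/32) = 0.99 SD.

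If the SD of six-month change is 0.2–0.6 (assumption), these are 0.14–0.42, 0.10–0.30 and 0.20–0.59 Z.

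**The case against.** The strongest reply is that the trial is larger than its inputs require. That is correct: 40 exceeds 27–28, and 32 completers give 93 % power on the stated inputs. The arithmetic gap is then an unexplained step in a condensed article and does no harm by itself. A reader might infer from this point that the trial is underpowered, but the documents do not show it. Under the assumed SDs above, power runs from poor to ample, and no Z-scale effect is given against which to judge it.

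Four other stronger readings should be resisted.

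- That 2.29 cannot be a Z-score SD. The cited tables are not at hand, and very obese children on another reference may be more spread than 0.37. The entry cut-off and the endpoint also use different references, so z > 1.645 is only approximate for the endpoint. The objection to the 2-unit difference does not depend on those tables.
- That the Background supports a small BMI effect. Its remark about modest improvement concerns insulin sensitivity; it gives no size for BMI.
- That six-pair Bonferroni is where the 40 came from. It is one candidate among several, fails with the t-test, and includes pairs that cross both puberty and treatment and answer no trial question.
- That power for the puberty interaction is misstated. The abstract announces "This study will assess the differential response of metformin treatment at six months in pre-pubertal and pubertal obese children", but the Sample size section makes no power claim for it and the four numbered objectives do not list it. That is an omission, and power figures for it on the 2.29 scale would inherit the disputed inputs.

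**Conclusion.** Two defects stand. The main one is scale: an SD of 2.29 and a 2-point difference, assigned to the BMI Z score, are not credible for this population. The SD is also credited to reference 29 while the endpoint is computed on reference 31. Raw BMI units are the likely explanation, but this is an inference. The 80 % power statement therefore has no support for the primary endpoint, whether the true power is higher or lower.

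The second is reproducibility: the stated inputs give 21–22 evaluable and 27–28 recruited per group against a stated 40. This shortens no margin, since the stated number is the larger.

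The arithmetic assumes a two-sided test of two equal groups; a one-sided test moves the answer further from 40. The scale argument assumes an approximately normal reference and a baseline a little above the entry cut-off. The scale of the inputs must be corrected because the primary endpoint rests on it; the origin of the 40 and the detectable differences are clarifications to make in the same revision.

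**What to change.** Keep 160 children and rewrite the Sample size section:

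- State the unit and source of the SD and of the difference, the sidedness, and the comparison being powered.
- Redo the calculation for six-month change in BMI Z score on the Spanish reference. Take the SD of change from an external source, or from a blinded pooled estimate in children already followed. In the latter case, say explicitly that it is not an interim efficacy analysis, because the section on interim analyses says that no interim or preliminary analyses are planned.
- Correct the 40, or state the adjustment that leads to it.
- Add, labelled as a sensitivity statement and not as the design difference, what 32 completers per group detect at 80 % power: about 0.70 SD within a pubertal stratum, 0.50 SD overall and 0.99 SD for the treatment-by-puberty interaction. The design difference itself needs its own clinical justification and should not be derived from the available number.

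The cost is an SD estimate and rewritten text. No extra children and no unblinding are needed. The downside is that the stated power may change.

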### Statistical analysis

Data will be analyzed using SPSS software version 22 for Windows. Descriptive statistics for all outcomes will be determined. A Kolmogorov-Smirnov test will be used to test data normality. Data that are not normally distributed will be transformed by means of a log10 or square root for analysis. The homogeneity of variances will be determined with a Levene’s test. Normally distributed data will be reported as mean ± standard deviation (SD) and nonparametric data as median (range). The analysis selected to determine the effect of treatment is a linear mixed effects model (LMM), for which the center is considered covariance to adjust the statistical analysis. The fixed effects include time, treatment, adherence, puberty, sex, the interactions *time × treatment*, *time × treatment × puberty* and *time × treatment × sex*. A Bonferroni test will be used to assess the specific differences between the treatments.

Regarding genetic variations, linear regression will be performed to analyze differences in principal variable changes between genotypes and to evaluate independent associated factors.

Moreover, the raw microbiologic data are reported as relative abundances. Differences among times, treatments and puberty are compared using the Mann-Whitney *U* test. Finally, the clustering of the colonic microbiota in both of groups is calculated by a principal component analysis.

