**Methods/design:**

This is a randomized, prospective, double-blind, placebo-controlled, multicenter trial, which is stratified by puberty and sex. Eighty pre-pubertal (40 boys and 40 girls) and 80 pubertal non-diabetic obese children (40 boys and 40 girls) are being recruited in four Spanish Clinical Hospitals. The inclusion criteria to participate in the RCT include a Body Mass Index (BMI) above the 95th percentile and age 7–14 years. The pubertal stage is determined based on the Tanner criteria. Participants are assigned to two groups in accordance with a randomization schedule and receive 1 g of metformin or placebo for six months in combination with healthy lifestyle recommendations in both groups. The primary outcomes include changes in the BMI Z score and the biomarkers associated with the early appearance of insulin resistance syndrome, inflammation, cardiovascular risk according of the presence of genetic determinants of metformin response, as well as possible modifications in microbiota.

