### Participants

The study subjects comprise patients referred from the Pediatric Endocrinology Unit of the corresponding study centers. Children are eligible for this RCT if they meet the inclusion criteria (Table 2). The data are collected in the pediatric outpatient clinics by dieticians. The data and samples are codified according to each center and subsequently centralized at the Institute of Nutrition and Food Technology “José Mataix” (INYTA) in Granada, Spain.

**Table 2 Tab2:** Inclusion and exclusion criteria

Inclusion criteria	Exclusion criteria
BMI greater than the 95th percentile based on the standards set by Cole et al*.* [26]	Does not meet the established age
Age 7–14 years	Any previous underlying disease
No underlying disease or a history of pathology	Use of medication with metabolic side effects, such as diuretics, β-blockers, β-adrenergics, or corticoids
No medical treatment regarding weight control in the previous 12 months	Cases of monogenic obesity
No participation in a previous trial	Children subjected to long periods of rest
	Did not sign the informed consent

*BMI* Body Mass Index

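### The normality rule could move BMI Z score to a log10 or square-root scale, where equal falls in Z points can look like a different response by pubertal stage

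*Protocol article*

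**What the plan says.** All references are to the protocol article.

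- **Statistical analysis.** "A Kolmogorov-Smirnov test will be used to test data normality", and then "Data that are not normally distributed will be transformed by means of a log10 or square root for analysis". The object tested is the data; model residuals are not mentioned. No outcome is exempt, and nothing says when log10 or square root applies or what happens to values at or below zero. The treatment effect comes from a linear mixed model that includes time × treatment × puberty.
- **Abstract, Methods/design.** "The primary outcomes include changes in the BMI Z score", among others.
- **Sample size.** "As previously indicated, the principal variable is the BMI" *Z* score, and "a desired minimum difference of 2 points is expected", so the target is a difference in Z points.
- **Participants, Table 2.** Entry requires "BMI greater than the 95th percentile based on the standards set by" one set of cut-offs.
- **Anthropometry.** The outcome Z score is "calculated based on Spanish reference standards published by" a different source.
- **Abstract, Discussion.** Differential response by pubertal stage is the stated question.

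**The concern.** The rule looks at the wrong object. The time × treatment terms rest on within-child variation, and what should be roughly normal is the residual after time, treatment, puberty and sex are in the model. Raw BMI Z here is cut from below by eligibility and mixes two pubertal stages, so it can fail a normality test while those residuals are well behaved.

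The remedy also suits this outcome poorly. Zero on a Z scale is the reference mean, not an absence of the quantity. A log10 or square-root change depends on where the child started. Two strata with the same fall in Z points but different starting levels will show different changes on the new scale, and time × treatment × puberty tests exactly that difference. At stake are the trial's main subgroup question and the ability to report the effect in the units of its sample-size target.

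**Working it through.** **Inputs from the article.** Target difference 2 Z points; SD 2.29; 40 children per treatment-by-puberty group; 20% loss, hence 40 × 0.80 = 32 completers per cell and 4 × 32 = 128 in all; entry above the 95th percentile, which is Z ≈ 1.645. The article gives no figure for the transformation rule. Its only computed figure is the 40 per group. The stated inputs give 2 × 2.29² × (1.960 + 0.842)² / 2² ≈ 20.6, so 21, and 21/0.80 rounds up to 27. The 40 is therefore not reproduced, but nothing below depends on that beyond the cell size.

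**Assumed, because the article does not give them.** Baseline Z distributions by stage, a change SD of 0.25, and equal falls of 0.3 to 0.5 Z on metformin in both stages.

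**Step 1: can the rule fire?** Normal distributions cut at 1.645, n = 160, 400 runs each:

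| Parent mean, SD | Mean after cut | Skewness | Lilliefors-corrected K-S rejects | Uncorrected K-S rejects |
|---|---|---|---|---|
| 0, 1 | 2.06 | 1.46 | 100% | 98.5% |
| 1, 1 | 2.25 | 1.21 | 100% | 85% |
| 2, 1 | 2.59 | 0.86 | 95% | 28% |
| 3, 1 | 3.17 | 0.45 | 28% | 0.5% |
| 1.645, 2.29 | 3.47 | 1.00 | 99% | 55% |
| 3, 2.29 | 4.06 | 0.75 | 83% | 13% |

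Rejection is near certain when children cluster just above the cut, and uncommon when the mean lies far above it relative to the spread.

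**Step 2: what the transform does to equal falls.** For a fall d from baseline a, the change is log10((a − d)/a) or √(a − d) − √a.

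- d = 0.3 from 3.0: log10(2.7/3.0) = −0.0458; √2.7 − √3.0 = −0.0889.
- d = 0.3 from 2.5: log10(2.2/2.5) = −0.0555; √2.2 − √2.5 = −0.0979.
- Ratios: 0.0555/0.0458 = 1.21 (log10) and 0.0979/0.0889 = 1.10 (square root). For 3.5 against 2.5 they are 1.43 and 1.19. For equal baselines they are 1.00.
- d = 2 from 4.0 and 2.5: log10(2/4) = −0.301 and log10(0.5/2.5) = −0.699, ratio 2.3.

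**Step 3: the whole rule.** Test first, transform only on rejection, then test the treatment-by-puberty contrast of change at nominal 5%. There are 32 per cell, the true effect is equal in both stages, and locations are those of the parent normals before the cut. Ranges cover both K-S versions and both falls.

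| Assumed stage locations | log10 | Square root |
|---|---|---|
| 3.5 vs 2.3 | 11-43% | 7-17% |
| 3.0 vs 2.3 | 4-15% | 4-7% |
| 2.6 vs 2.3, or equal | about 5-6% | about 5-6% |

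A repeat run (K-S on pooled baseline, n = 128; pre-pubertal SD 1.0, 0.8 or 0.7 and pubertal SD 0.6) agreed to within about two percentage points. Left untransformed, the contrast rejected 5.0-5.9% of the time in a separate simulation of ten scenarios.

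**Step 4: no treatment effect.** With a zero fall and unequal baselines (means 3.18 and 2.25), rejection was 5.1% on Z, 5.2% on log10 and 5.2% on square root.

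**Step 5: undefined values.** A fall of 2 points takes any child entering at Z ≤ 2 to Z ≤ 0, where log10 does not exist; below 0 the square root fails too. In assumed distributions, 8-54% of treated children would be affected. With falls of 1 point or less, essentially none would be. If the rule were applied to change scores, a fall is negative and neither transform is defined.

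**The case against.** The strongest reply is that this is a condensed article in which one generic sentence covers every outcome, including positive, skewed biomarkers for which a log is sensible. Residual checks and outcome-specific handling normally sit in an analysis plan that is not shown. That lowers the weight of the point but does not remove it: the article states a rule, without exemption, that reaches the principal variable.

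It can also be said that the rule may not fire. The article does not say which K-S version applies or whether testing is pooled. In assumed scenarios tested within each group of 32, the Lilliefors version rejected only 8-10% of the time. That stands, and is why whole-rule rates are given.

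Four stronger readings may tempt a reader, and the documents support none of them:

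- *That error rates computed on log10 alone are the trial's error rates.* Those (for example 41.4% for a 0.5 fall at baseline means 3.17 and 2.25) assume that the rule fires and that log10 is chosen. The article also allows the square root, which does less harm (16.9% in the same case).
- *That the primary treatment test becomes invalid.* In a randomised comparison, no effect on Z is also no effect on log10 or square-root Z, and step 4 confirms it.
- *That both transforms turn the question into one about ratios.* Only the log does; a difference of square roots is not a ratio.
- *That baseline outcome Z is sharply cut at 1.645.* Eligibility and outcome use different references, so the cut is approximate.

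**Conclusion.** The point holds as a conditional one. The rule tests the wrong object and, if it fires for BMI Z, gives an effect that cannot be stated in Z points or set against the 2-point target. That loss of interpretation needs no assumption about pubertal stage.

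A false pubertal difference needs three things together: the normality test rejects, metformin has an effect, and mean baseline Z differs by stage. Stratifying by puberty does not make baseline Z equal across strata, but the article gives no stage means, so the gap is assumed. For the largest gap tried the inflation is material under either transform. For the middle gap it ranges from none to about three times nominal with log10 and is slight with the square root. For a small or absent gap it is negligible. Undefined logs matter only if falls approach the planned 2 points.

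**What to change.** In the Statistical analysis section:

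1. State that BMI Z score is analysed untransformed in the linear mixed model, with residual plots and, if residuals look poor, a bootstrap or robust-standard-error sensitivity analysis.
2. Remove the K-S-triggered transformation for BMI Z.
3. For positive, skewed biomarkers (such as insulin, HOMA-IR, triglycerides and cytokines), fix log transformation in advance and check model residuals instead of raw data.

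The cost is a few sentences. It needs no extra patients or data, and it can be settled before unblinding, since the article reports recruitment as still under way.

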**Fig. 1 Fig1:**
[figure not shown]
Participant flow diagram. *PPG* pre-pubertal girls; *PPB* pre-pubertal boys; *PG* pubertal girls; *PB* pubertal boys

**Table 1 Tab1:** Distribution of patients according to center

Hospital	Total (160)
Reina Sofía (Córdoba)	20 pre-pubertal girls
	20 pre-pubertal boys
Virgen de las Nieves (Granada)	10 pre-pubertal girls
	10 pre-pubertal boys
	10 pubertal girls
	10 pubertal boys
Clínico Universitario (Santiago de Compostela)	10 pre-pubertal girls
	10 pre-pubertal boys
	10 pubertal girls
	10 pubertal boys
Lozano Blesa (Zaragoza)	20 pubertal girls
	20 pubertal boys

Children are randomly assigned to receive metformin or placebo for six months. Both treatments are administered during meals (to minimize gastrointestinal side effects and the risk of hypoglycemia). The participants’ parents are given a coded vial of pills that contains either metformin or placebo pills for two months. The concealed allocation process ensures that the participants and all investigators are unaware of the allocated treatment. All participants are offered lifestyle intervention advice at all visits.

The clinical hospitals that participate in the RCT form part of the Maternal and Child Health and Development (SAMID network). Moreover, the RCT has been registered in the European Clinical Trials Database on 14 November 2011 (EudraCT, ID: 2010-023061-21).

In accordance with the “International Conference on Harmonization of Technical Requirements for Registration of Pharmaceuticals for Human Use” Guide (ICH): “CPMP/ICH/291/96 Note for Guidance on General Considerations for Clinical Trials,” this is a phase III clinical trial because it involves a commercialized drug for which a new indication that is not included in its technical specifications will be investigated.

The CONSORT statement (Consolidated Standards of Reporting Trials) has been taken into account in the study design report, as well as for the abstract and the flow diagram (Fig. 1), thereby increasing the reporting quality for the RCT. Moreover, the Standard Protocol Items: Recommendations for Interventional Trials (SPIRIT) guidelines for this study protocol are attached in Additional file 1.

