### Interventions

The patients are instructed to taking a initial dose of 50 mg twice daily for 10 days, followed by 500 mg twice daily until the end of the treatment. The presentation comprises tablets in opaque, white plastic containers and a side label with 28 units. The dietician centers administer a food frequency questionnaire (FFQ) and a physical activity survey to all participants at the beginning and at the end of the trial. All participants are provided with standardized healthy lifestyle advice at the start of a one-on-one session, including a healthy diet and exercise advice sheet. The participants attend an initial trial baseline visit, followed by three additional visits at 2-month intervals (Fig. 2), which include anthropometric parameter and blood pressure (BP) assessments, as well as a physical examination. A medical history is obtained for each participant, including documentation of the family history.

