### Adverse effects and co-medication

To assess the safety of metformin administration, the primary evaluation criteria are the absence of the adverse effects (AEs) described. The patients are assessed regarding all symptoms at each visit to identify potential AEs and the use of co-medication in the previous two months. A contact number is provided to enable enquiries regarding any symptom perceived as adverse. At this number, the patient is informed about what to do in the event of an adverse reaction. They are also requested to suspend the medication. The following information is recorded: description, date of onset and end date, severity, assessment of relation to the study medication, other suspect drug or device and action taken. Follow-up information should be provided as necessary. The prominent AEs are as follow: diarrhea, nausea, blood in the stools, headache, dizziness, general discomfort, sleepiness, cold or flu, pharyngitis, otitis, allergic episode, lactic acidosis, urea increment, hypercreatininemia, hypertransaminasemia and vitamin B_12_ deficiency, as well as any other symptoms reported by the participants. The relationships of the AEs to the study medication will be assessed by a qualified medical investigator.

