### Adherence and tolerance

Adherence will be measured as a percentage using the following formula:$$ \mathrm{Quick}=\left(\left(\mathrm{Pillsingested}{\textstyle \hbox{-}}\mathrm{pillsreturned}\right)/\mathrm{Pillspredicted}\right)\times 100 $$

These data will also be taken into account for statistical analysis as fixed effects. Tolerance is reported as the descriptive statistics of the adverse effects in relation to the achieved dosage level.

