In view of this situation, our research could provide consolidated evidence regarding metformin’s effects on obese children, considering the pubertal stage via homogeneous Tanner stratification, as well as finding possible lines of action by metformin. Nevertheless, the study has several limitations, including the difficulty of assessing treatment compliance in children, as well as lifestyle changes. Moreover, the supervision of dietary habits and physical activity proves rather complicated. We are controlling for medication taken by means of the delivery and return of the bottles; however, we are aware that this strategy does not ensure accuracy regarding intervention compliance information.

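### Adherence, measured after randomisation and open to influence by treatment, is a fixed effect in the only stated treatment-effect model; which contrasts it biases depends on an unstated form of entry

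*Protocol article*

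**What the plan says.** All references are to the Protocol article.

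- **Statistical analysis** commits to one model for the treatment comparison: "The analysis selected to determine the effect of treatment is a linear mixed effects model (LMM". Its terms are then listed: "The fixed effects include time, treatment, adherence, puberty, sex, the interactions" of time with treatment, alone and with puberty or sex. No adherence × time term is listed. Bonferroni comparisons between treatments follow.
- **Adherence and tolerance** gives a pill-count percentage and adds: "These data will also be taken into account for statistical analysis as fixed effects".
- **Discussion** describes the source of the data: "We are controlling for medication taken by means of the delivery and return of the bottles".
- **Adverse effects and co-medication** says of patients who report an adverse reaction: "They are also requested to suspend the medication".
- **Study design**, below Table 1, anticipates gastrointestinal effects: "Both treatments are administered during meals (to minimize gastrointestinal side effects and the risk of hypoglycemia".
- **Interventions** sets a baseline visit, "followed by three additional visits at 2-month intervals".

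No treatment-effect analysis without adherence is stated for the principal variable, the BMI Z score.

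**The concern.** The first objective is to compare metformin plus lifestyle with placebo plus lifestyle on BMI after six months. Randomisation protects that comparison only while the model conditions on nothing that treatment can change. Adherence fails this test, because the article itself gives two routes from drug to adherence: gastrointestinal effects, and suspension after a reaction.

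Two things can go wrong. Holding adherence equal between arms sets aside any benefit lost through intolerance, although that loss is part of the effect being asked about. Also, family engagement plausibly raises both pill-taking and the response to lifestyle advice. At a given level of adherence, metformin children would then be more engaged on average than placebo children, and the adjusted contrast would credit the drug with that engagement.

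**Working it through.** **1. Status of the variable.** Pill counts from returned bottles exist only after treatment starts, so adherence is a post-randomisation variable. Two sections place it among the fixed effects of the treatment model. The plan states no figure on this point, so there is none to reproduce.

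**2. What the stated model does.** Adherence enters as a main effect only, so the result depends on the form of entry.

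*One value per child.* A value that is constant over a child's visits cannot explain change within the child. With complete data, time × treatment is therefore unaffected. The treatment main effect moves by

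shift = −(slope of the child's mean BMI Z on adherence, within arm) × (adherence on metformin − adherence on placebo),

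and every adjusted between-arm mean moves with it, including the one at baseline.

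*One value per visit.* Adherence now varies within the child, so the time × treatment estimate moves as well. No adherence value exists at baseline: left blank, the baseline rows drop out; otherwise a value must be supplied.

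**3. Size under assumptions.** None of these inputs is in the documents:

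- true month-6 effect −0.20 Z, reached linearly over four visits;
- mean adherence 90 on placebo, and 0, 5, 15 or 25 points lower on metformin;
- one SD of unmeasured motivation raises adherence by 5 points and lowers month-6 Z by 0.10;
- other variation in adherence has SD 8, and values are capped at 0 and 100;
- correlation between visits 0.7, with 200,000 children so that sampling error is small.

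The model is a random-intercept fit with time as a factor. Puberty, sex and centre are left out. Estimates in BMI Z:

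| Adherence deficit on metformin (points) | No adherence term: month-6 time × treatment | Per visit: month-6 time × treatment | Once per child: month-6 time × treatment | Once per child: treatment main effect | Once per child: adjusted month-6 difference |
|---|---|---|---|---|---|
| 0 | −0.203 | −0.203 | −0.203 | 0.005 | −0.199 |
| 5 | −0.203 | −0.212 | −0.203 | −0.003 | −0.206 |
| 15 | −0.200 | −0.234 | −0.200 | −0.044 | −0.244 |
| 25 | −0.204 | −0.258 | −0.204 | −0.067 | −0.271 |

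Measured against the assumed −0.20, the affected contrast moves by about 0, 0.01, 0.03–0.04 and 0.06–0.07 Z. Averaged over eight repeat runs and compared with the fit without adherence on the same data, the per-visit shifts are 0, 0.010, 0.032 and 0.055, and the once-per-child shifts are 0, 0.014, 0.041 and 0.070. In the per-visit fit, giving every child the same baseline value, 0 or 100, made no difference because time is a factor.

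**4. Check by hand (once per child, ignoring the cap).** The within-arm slope of motivation on adherence is 5/(5² + 8²) = 5/89 = 0.0562 SD per point. The visits sit at 0, 1/3, 2/3 and 1 of follow-up, so motivation changes the child's mean Z by −0.10 × 0.5 = −0.05 per SD. The slope of mean Z on adherence is −0.05 × 0.0562 = −0.0028 per point. The shifts are −(−0.0028)(−5) = −0.014, −(−0.0028)(−15) = −0.042 and −(−0.0028)(−25) = −0.070. These agree with the simulation.

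**The case against.** The strongest defence is that time × treatment is the term that tests a difference in BMI Z change, and the article gives a single percentage formula with no mention of visit-level values. One value per child is then at least as natural a reading, and under it that term is essentially untouched with complete data. This stands. A reader might infer that the whole treatment effect ceases to be the randomised comparison; the documents do not support that. What remains is that the treatment main effect and the adjusted means are conditional on adherence, that the Bonferroni comparisons may use those means, and that per-visit entry is not ruled out.

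A reader might also size the problem by regressing six-month change on treatment and adherence. Under the same assumptions this gives −0.23, −0.29 and −0.35 at deficits of 5, 15 and 25 points, so shifts of 0.03, 0.09 and 0.15 Z. That is not the model described, and it overstates the shift about two- to threefold.

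The arms may also differ little in adherence. Dosing with meals and a lower starting dose may limit any gap, and withdrawn children are already excluded. With no gap there is no shift. This is fair, but it depends on data not yet seen.

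The Discussion concedes of pill counts that "we are aware that this strategy does not ensure accuracy regarding intervention compliance information". This concerns measurement error, not conditioning on a post-randomisation variable, and does not support the point. Random error would generally weaken the adherence slope and so reduce the shift.

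Finally, an article condenses a fuller document, and an analysis without adherence could appear there. The adherence term is nevertheless a positive choice made in two sections, not an omission.

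**Conclusion.** The point holds in this limited form. Adherence does not belong among the fixed effects of the model that defines the treatment effect. Entered once per child, it makes the treatment main effect and the adjusted between-arm means conditional on adherence, and leaves time × treatment essentially intact with complete data. Entered per visit, it biases time × treatment as well.

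The documents do not give the size. The shift is zero if the arms adhere equally and, on the assumptions shown, grows to about 0.06–0.07 Z at a 25-point deficit, against an assumed effect of −0.20 Z. The direction, in favour of metformin, rests on two assumptions: adherence is lower on metformin, and children who adhere better also improve more for reasons other than the drug.

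A reader might conclude that deleting the term restores the full randomised comparison. It does not: Interim analyses and stopping rules excludes the data of withdrawn children, which is a separate departure based on an event after randomisation.

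**What to change.** In Statistical analysis, delete adherence from the fixed effects of the primary mixed model. In Adherence and tolerance, replace the sentence on fixed effects with a statement that adherence will be summarised by arm and will not enter the primary model. If an analysis using adherence is wanted, label it supportive and state whether adherence enters once per child or per visit and, if per visit, how baseline is handled.

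The cost is one model term and one sentence, with no new data and no change to the sample size. Recruitment was continuing and the data analysis is planned to be blinded, so the change can be made before unblinding. The exclusion of withdrawn children needs its own decision.
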